##### Accelerometer

Participants will receive an accelerometer ActiGraph GT9X Link (ActiGraph LLC, Pensacola, FL, USA) and wear it for 7 consecutive days on the non-dominant wrist. Sleep time, sedentary time, and physical activity will be registered with the accelerometer.

### Cost-effectiveness analysis

The economic analysis will be conducted from the perspective of the healthcare system with the objective of estimating the approximate cost of implementing this exercise program for this population. This analysis will include healthcare utilization and intervention costs. The health system cost will be recorded, including the visits of physicians and nurses in primary care, specialist physicians, physiotherapists, social workers, occupational therapists, and dietitian services; medication use; emergency rooms; hospital days; diagnostic imaging tests; blood tests; and metagenomics. Furthermore, the costs of the intervention will be estimated based on records of the time spent by exercise instructors, the use of sports facilities, and the purchase of exercise equipment. The time frame for the analysis will be approximately 6 months.

Two types of economic analysis will be conducted: an intention-to-treat and a per-protocol analysis. The intention-to-treat analysis will include all participants who will complete the trial, whereas the per-protocol analysis will include only those participants who will attend at least 70% of the exercise sessions.

To calculate the incremental cost-effectiveness ratio (ICER), we will examine the differences in costs and effectiveness between the intervention and control groups. Specifically, the incremental cost per participant will be divided by the incremental effectiveness to get the ICER. The ICER will be calculated for the incremental cost per person required to improve the health-related quality of life (HRQOL, assessed through Euroqol-5D [EQ-5D]) and functional capacity (assessed through Short Physical Performance Battery [SPPB]), and reduction of excess weight loss (%) and fat mass (%).

Finally, non-parametric bootstrap techniques of costs and health outcomes will be employed to estimate the probability that an exercise intervention would be cost-effective given a decision-maker’s willingness to pay for each additional unit of health outcome gained, or excess weight loss and fat mass reduced. Furthermore, cost-effectiveness acceptability curves will be presented, illustrating the probability of exercise intervention in this population could be cost-effective compared with the control group.

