## Material and methods

### Study design, research ethics approval, protocol registration, and reporting

This protocol is a two-arm superiority randomized controlled trial. It has been registered in Clinicaltrials.gov NCT05695599 and approved by the Ethics Committee of Clinical Research of Aragón (CEICA, Spain) with reference number C.I. PI22/380. In the event that changes to the protocol are necessary during its implementation, permission will be sought from the Ethics Committee before applying the changes. Participants will be randomly assigned to one of two groups: (1) the control group (CG) or (2) the WBV group. The study design and this protocol manuscript adhere to the SPIRIT reporting guidelines and the SPIRIT 2013 checklist is presented in Supplementary Table 1 [27]. Moreover, the exercise intervention is explained in accordance with the Consensus on Exercise Reporting Template (CERT): Explanation and Elaboration Statement [28]. The 16 items that should be completed in accordance with the CERT are presented in Supplementary Table 2.

As illustrated in Fig. 1, the study will span a period of 18 months. Four different assessments will be conducted at various intervals: T1 (approximately 1 week before the surgery), T2 (7 ± 1 weeks post-surgery), T3 (24 ± 2 weeks post-surgery), and T4 (18 months ± 2 weeks post-surgery).

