### Statistical methods

The Shapiro–Wilk test will be used to test for normality of the data while variance homogeneity and sphericity will be assessed with the Levene and Mauchly tests, respectively. To assess changes over time in the assessed outcomes, a repeated-measures ANOVA with Bonferroni correction will be used to assess the interaction between group (control group vs. WBV) and time (baseline vs. 2nd vs. 3rd vs. 4th assessments). In the absence of a normal distribution, data will be analyzed with the Wilcoxon test for within-group comparisons and the Mann–Whitney test for between-group comparisons using Bonferroni’s correction. To test for associations between variables, both correlations and linear regressions will be performed. The significance level will be set at 5%. Per-protocol and intention-to-treat analyses will be performed in order to account for the possible dropouts during the study. In the per-protocol analysis, we will include only the participants who attend at least 70% of the sessions and undergo the baseline and post-intervention outcome assessments. For the intention-to-treat analysis, we will consider all the participants who will undergo the baseline assessments and subsequently participate in at least one additional assessment following their group assignment will be considered.

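### The economic intention-to-treat set is defined as trial completers, which conflicts with the trial's own intention-to-treat set and may discard usable 6-month data

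*Protocol article*

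**What the plan says.** The protocol article defines an intention-to-treat (ITT) population twice.

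- **Cost-effectiveness analysis:** "The intention-to-treat analysis will include all participants who will complete the trial".
- **Statistical methods:** the ITT set is "all the participants who will undergo the baseline assessments and subsequently participate in at least one additional assessment following their group assignment".

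The economic section also says "The time frame for the analysis will be approximately 6 months". The study design section says that "the study will span a period of 18 months", with T3 at 24 ± 2 weeks and the last visit given as "T4 (18 months ± 2 weeks post-surgery". The article does not say which visit marks completion of the trial.

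Two further phrases in the economic section need attention. The "per-protocol analysis will include only those participants who will attend at least 70% of the exercise sessions", with no mention of arm, although only the whole-body vibration (WBV) group is offered sessions. The listed effects for the ICER include "reduction of excess weight loss (%) and fat mass" (both in percent).

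**The concern.** An ITT analysis is meant to keep participants in their assigned arm whether or not they stay to the end. Restricting it to completers removes the people the label promises to keep. The clinical and economic results would then both be called ITT but describe different people.

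This can matter for the economic result. WBV sessions are supervised one to one and instructor time is a counted cost. A participant who attends some sessions and then leaves has used resources, perhaps with little gain. Dropping that person removes cost without removing benefit, which tends to make the programme look better value. The Discussion says that a positive economic result would lead the researchers to seek funding for an extension and to try to have the programme included in usual care.

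**Working it through.** **Inputs.** From Sample size: 24 evaluable participants, 15% attrition, 28 recruited (14 per group). From Training frequency, intensity, and duration: 47 sessions. From Study design: T3 at 24 ± 2 weeks, T4 at 18 months. From Cost-effectiveness analysis: a horizon of about 6 months.

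**The plan's own figure.** 24 × 0.15 = 3.6, and 24 + 3.6 = 27.6, rounded up to 28. This matches the article, and the point below does not depend on it.

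**Size of the two ITT sets at planned attrition.**

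- Economic set (completers): 28 × 0.85 = 23.8, about 24. Removed: 28 × 0.15 = 4.2, about 4.
- Clinical set: up to 28, if every dropout has at least one assessment after assignment.

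**Horizon.** A participant who attends T1 to T3 and misses T4 has the visits that cover about 6 months. If completion means T4, this person is excluded from a 6-month analysis because of a visit about a year after the horizon closes. If completion means T3, this exclusion disappears. The set is still one of completers, and it still differs from the clinical set, which admits someone seen at baseline and T2 only.

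**Possible effect on the ICER (illustration, with assumed values).** Suppose 2 of 14 WBV participants drop out. Let completers have mean incremental cost C and effect E against control. Let each dropout incur a fraction c of C and gain a fraction b of E, and leave the control means unchanged.

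- ICER in completers: C / E.
- ICER in all 14: [(12 + 2c)C / 14] / [(12 + 2b)E / 14] = (C / E) × (12 + 2c) / (12 + 2b).
- Ratio, completers to all: (12 + 2b) / (12 + 2c).

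| c | b | Ratio | ICER understated by |
|---|---|---|---|
| 0 | 0 | 12/12 = 1.000 | 0% |
| 0.25 | 0 | 12/12.5 = 0.960 | 4% |
| 0.5 | 0 | 12/13 = 0.923 | about 8% |
| 1 | 0 | 12/14 = 0.857 | about 14% |
| 1 | 0.5 | 13/14 = 0.929 | about 7% |
| 0.5 | 0.5 | 13/13 = 1.000 | 0% |

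If b exceeds c, the direction reverses.

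**Attendance rule.** 70% of 47 is 32.9, so 33 sessions. Control participants are offered none. Read literally, 0 of 14 controls qualify and no difference between arms can be formed. The per-protocol rule in Statistical methods has the same gap.

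**Direction of the weight effect.** With an assumed extra cost of 500 and 5 points more excess weight lost, the ICER is 500 / 5 = +100 per point. Scored as a reduction in excess weight loss, it is 500 / (−5) = −100.

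**The case against.** The strongest reply is that most of this is loose wording in a condensed article. Several stronger readings are indeed tempting, and the documents do not support them.

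- **That the completer rule flatly contradicts the 6-month horizon.** Completion is not defined. In a section with a 6-month time frame it may mean T3, so the conflict is conditional.
- **That the per-protocol analysis has no controls.** The same section forms the ICER from differences between intervention and control, and only the WBV arm is offered exercise. The evident intent is that the attendance rule applies to that arm.
- **That the weight effect would be scored backwards.** The sentence concerns the cost of improving outcomes, and the Conclusions expect greater fat loss with WBV. This is a slip of phrasing.
- **That the ICER will be understated by 14%.** That is one end of a range. It assumes two WBV dropouts, full average cost and no benefit, none of which the article states. The 15% is an overall planning figure, not one for each arm. The calculation also models early dropouts. People who leave between T3 and T4 may have finished the programme, and excluding them has no predictable direction of bias.
- **That this result decides adoption.** The Discussion says only that the researchers would seek funding and would attempt inclusion in usual care. Cost-effectiveness is not among the primary outcomes.

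It is also fair that a method for missing economic data commonly sits in a fuller plan, so its absence here is no fault. What remains is what the article does state: a completers' set called ITT, alongside a different set with the same name.

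**Conclusion.** The economic ITT definition is wrong as written, because it describes completers and conflicts with the definition in Statistical methods. This rests on the text alone. At the planned 15% attrition it would exclude about 4 of 28 participants. The loss of people with full 6-month data follows only if completion means T4, which is the plain reading of an 18-month study but is not stated.

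The effect on the ICER is illustrative: 0% to about 14% understatement with two of 14 WBV dropouts gaining nothing, and less with partial benefit. The attendance rule and the weight effect are wording corrections, not analytic errors. The change should be made, but it does not touch the primary outcomes.

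**What to change.** 1. Define the economic ITT set as all randomised participants, analysed in their assigned arm over T1 to T3. State how missing 6-month costs or effects are handled, for example by multiple imputation combined with the planned bootstrap.
2. Report the completers' set only as a sensitivity analysis under that name, and say which visit defines completion.
3. Choose one ITT definition. All randomised is wider than the set in Statistical methods, which requires a later assessment, so the plan cannot adopt both under one label. Either align the clinical definition or give the two sets different names.
4. In both sections, state that the 70% attendance rule applies to the WBV arm only, and that controls are kept if they have the required assessments.
5. Write the weight effect as percent excess weight lost, higher being better, and use the same wording in the bootstrap paragraph.

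The cost is a few sentences and a modest amount of extra analysis, with no new data. The drawback is that imputation of this kind relies on a missing-at-random assumption, which the completers' sensitivity analysis does not test fully.

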### Participants

#### Sample size

The sample size for the present study was calculated using G*POWER 3.1. The F-test family, repeated measures, within-between interaction for two groups and four measurements was selected, assuming a correlation among the repeated measurements of 0.5. A total of 12 participants per group were required to achieve a power of 80% with a significance level of 5% under the assumption that we would find small-medium effect sizes (partial eta square of 0.06). This would entail a total of 24 participants. In the event of a 15% attrition rate during the experiment, it would be necessary to recruit an additional 3.6 participants. Consequently, the final study sample would be of 28 participants (14 per group).

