### Outcome variables

The primary outcomes will be (1) body composition, (2) results obtained from the adapted Bruce protocol, (3) basal metabolic rate, and (4) perceived quality of life. All the other variables will be considered as secondary variables. Both primary and secondary outcomes are explained in detail below.

All tests will be conducted in the GENUD-Lab, with the exception of the blood and stool collection, which will be performed at Clinico Lozano Blesa Hospital (situated a 5-min walk from the GENUD-Lab). The outcome variables will be assessed at four different time points (see Fig. 1 or 3). In each time point, participants will attend the laboratory on two different days, with less than a week between them. On each day, different variables will be collected, as detailed below.

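### The ICER names no baseline adjustment of the effect measures; regressing each on its pre-surgery value would make the incremental effect more precise at almost no cost

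*Protocol article*

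**What the plan says.** The Cost-effectiveness analysis section starts from group differences: "we will examine the differences in costs and effectiveness between the intervention and control groups". It continues: "Specifically, the incremental cost per participant will be divided by the incremental effectiveness to get the ICER". Uncertainty is handled by resampling: "non-parametric bootstrap techniques of costs and health outcomes will be employed to estimate the probability that an exercise intervention would be cost-effective", followed by acceptability curves. The horizon is short: "The time frame for the analysis will be approximately 6 months".

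There are four effect measures: EQ-5D, the Short Physical Performance Battery (SPPB), excess weight loss and fat mass. Some of the wording suggests change rather than a follow-up value: "The ICER will be calculated for the incremental cost per person required to improve the health-related quality of life", "and reduction of excess weight loss (%) and fat mass". The section does not define effectiveness as either, and it names no regression or covariate.

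Baseline data exist. The Outcome variables section says: "The outcome variables will be assessed at four different time points". The first of these, T1, falls about a week before surgery. The SPPB is not listed as a test of its own, but balance stances, a timed 4 m walk and five sit-to-stands are. Under Randomization, allocation and blinding, sex is the only factor that allocation takes into account. The Statistical methods section includes baseline as one level of time in its repeated-measures ANOVA, but nothing links that model to the ICER.

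**The concern.** The economic method is set out step by step, from group differences to ratio to bootstrap, and no step uses the baseline value. In a trial of 28 people with allocation balanced only on sex, the arms will often differ at baseline on quality of life, function, weight or fat mass. Part of such a gap then enters the denominator of the ICER. A ratio with a small, noisy denominator is sensitive to this, and so is the acceptability curve built from the same increments.

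The result has a stated use. The Discussion says that a favourable cost-effectiveness finding would lead the researchers to seek funding for longer follow-up and more participants.

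**Working it through.** **Inputs.** 12 evaluable and 14 recruited per arm, and partial eta squared 0.06 (Sample size section). Correlation, same section: "assuming a correlation among the repeated measurements of 0.5". The documents give no correlation for EQ-5D, SPPB, excess weight loss or fat mass. I therefore take 0.5 as an assumption and show 0.3 to 0.8. All effects are in between-person SD units with equal variance at each visit.

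**1. The plan's own figure.** The economic section states no number, so I checked the sample size. For the within-between interaction, f² = 0.06/0.94, λ = f² × N × 4/(1 − 0.5), with 3 and 3(N − 2) degrees of freedom. Power is 0.825 at N = 24 and 0.784 at N = 22, so 24 is reproduced. Adding 24 × 0.15 = 3.6 gives 27.6, rounded to 28.

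**2. Size of chance baseline gaps, 14 per arm.**
- SD of the difference in means = √(2/14) = 0.378.
- 95% range = ±1.96 × 0.378 = ±0.74.
- Mean absolute size = 0.378 × √(2/π) = 0.30.
- Probability that the gap exceeds 0.5 SD in either direction = 0.19.

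**3. How much of a gap d enters the incremental effect (correlation ρ).**
- Follow-up values: +ρd, which is +0.5d at ρ = 0.5.
- Change scores: −(1 − ρ)d, which is −0.5d at ρ = 0.5.
- Regression on baseline: about 0.

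In 40,000 simulated trials (14 per arm, ρ = 0.5) the slopes on d were +0.497, −0.503 and −0.005. All three estimators averaged about zero when the true effect was zero. A gap of 0.5 SD would therefore move the increment by about 0.25 SD, in opposite directions under the two unadjusted readings.

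**4. Standard error of the incremental effect, 14 per arm.** The formulas are √(2/14) for follow-up values, √(2/14) × √(2(1 − ρ)) for change scores, and √(2/14) × √(1 − ρ²) for regression on baseline. The last column multiplies by √(1 + 1/24) to allow for estimating the slope.

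| ρ | Follow-up | Change | Adjusted | Adjusted, slope estimated |
|---|---|---|---|---|
| 0.3 | 0.378 | 0.447 | 0.361 | 0.368 |
| 0.5 | 0.378 | 0.378 | 0.327 | 0.334 |
| 0.7 | 0.378 | 0.293 | 0.270 | 0.275 |
| 0.8 | 0.378 | 0.239 | 0.227 | 0.231 |

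At ρ = 0.5 the cut is 1 − 0.327/0.378 = 13%, or 1 − 0.334/0.378 = 12% with the slope estimated. The simulated SE of 0.335 gives 11%. At ρ = 0.3 the cut against follow-up values is 1 − 0.361/0.378, just under 5%, or 1 − 0.368/0.378, just under 3%, with the slope estimated. At every correlation in the table the adjusted SE is below both unadjusted ones, even after the slope allowance.

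**5. With 12 completers per arm, ρ = 0.5.** The SE is √(2/12) = 0.408 unadjusted and 0.354 adjusted, or 0.362 with the slope estimated: again a cut of 11 to 13%.

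**The case against.** The strongest reply is that nothing in the section is wrong. The quoted sentence is the ordinary definition of an ICER and fits adjusted increments as well as unadjusted ones. The article condenses a fuller document, and a health-economic plan that is not shown may already specify regression. This stands. A reader might infer that the plan divides raw differences, but the text never says raw or unadjusted. It only names no adjustment.

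Second, baseline is not ignored. Improvement and reduction suggest change scores, and excess weight loss refers back to pre-surgery weight by construction. This also stands, but change scores do not settle the matter. At correlation 0.5 they are no more precise than follow-up values and carry half the gap with the opposite sign. The exact equality holds only at 0.5. At 0.7 and 0.8 change scores come close to the adjusted analysis.

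Third, a reader might infer that the ICER is biased. In a randomised comparison each estimator of the increment is unbiased on average, and the bootstrap carries chance imbalance into its spread. The documents do not support a charge of systematic error.

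Fourth, a reader might want both T1 and T2 as covariates, since T2 precedes training. The text does not place randomisation after T2, so T2 may be a post-allocation value of a self-reported measure. It may also fall inside the six-month accounting window.

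Finally, gains expressed as power would be misplaced, because this section plans no hypothesis test. The standard error is the relevant scale.

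**Conclusion.** The point holds as an inexpensive gain in precision, not as an error in the plan. As written, the economic analysis names no baseline adjustment and leaves open two unadjusted definitions of effectiveness that respond to the same baseline gap in opposite directions. With 14 per arm, gaps of around 0.3 SD are ordinary. At correlation 0.5 about half of such a gap reaches the incremental effect. The cost is bias conditional on the imbalance that happens to occur, plus a standard error that one baseline covariate would cut by about 11 to 13%.

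The size rests on borrowing 0.5 from the sample size section. At 0.3 the gain over follow-up values is about 5% or less. At higher correlations it is larger against follow-up values and smaller against change scores. If a fuller economic plan already specifies baseline adjustment, all that remains is to say so.

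**What to change.** In the Cost-effectiveness analysis section, state that:

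- incremental effectiveness is estimated for each measure by regression on arm and the participant's own T1 value of that measure;
- for excess weight loss, whose T1 value is the same for everyone and cannot serve as a covariate, pre-surgery weight or BMI is used instead;
- participants are resampled within arm, and the regression is refitted in each bootstrap resample;
- the ICER and acceptability curves are built from these adjusted increments.

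With the T1 value in the model, analysing the follow-up value or the change from T1 gives the same arm effect, so the choice between those two definitions no longer matters. Add the T2 value only if it is confirmed that randomisation follows T2.

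The cost is a change of wording and one degree of freedom per effect measure. No new data are needed.

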### Data collection and management

Trained researchers will collect data from both the Clinico Lozano Blesa Hospital and the GENUD-Lab. All information collected during this trial will always be protected and securely stored by the lead researcher. The lead researcher will assign a secure locker in his office to store all investigation documents. Additionally, all electronic material will be safely stored and backed up on the researcher’s computer equipment with a secure password.

